### Data collecting, processing, and monitoring

2.7

All procedures for data collection and management will be conducted in accordance with the clinical research Standard Operating Procedures (SOPs) of each participating institution. For any procedures not specified in the institutional SOPs, the International Council for Harmonisation–Good Clinical Practice (ICH-GCP) guidelines will be followed. Study data will be entered into the CRF or electronic CRF (eCRF) immediately after the intervention. If any data are missing, the reason for the omission will be documented.

Collected data will be reviewed against source documents to ensure accuracy and consistency. All related study documentation will be archived to allow verification upon request after study completion. Documents containing personal identifiers will be securely stored in a locked facility for a minimum of 3 years, in accordance with institutional clinical research regulations. Electronic personal data will be encrypted and stored on secure systems.

Data monitoring will be conducted by designated research personnel at each site. The monitoring process will include routine verification of data entry accuracy, consistency, completeness, and compliance with the approved study protocol.

### Ethical considerations

2.8

#### Ethical approval

2.8.1

This study protocol has been reviewed and approved by the Public IRB designated by the Ministry of Health and Welfare, Republic of Korea (approval number: P01-202602-01-019). The study will be conducted in accordance with the ethical principles outlined in the Declaration of Helsinki and relevant national regulations governing clinical research involving human participants.

#### Informed consent

2.8.2

Prior to enrollment, all participants will receive a comprehensive explanation of the study objectives, procedures, potential risks and benefits, and data protection measures. Written informed consent will be obtained from all participants who voluntarily agree to participate after receiving and understanding this information. The informed consent process will be conducted in accordance with the approved IRB documents and the institution’s SOPs.

#### Management and compensation adverse events

2.8.3

In the event of a Serious Adverse Event(SAE) or medical emergency occurring during the study, participants will receive immediate and appropriate medical care in accordance with institutional clinical protocols. If an adverse event is determined to be related to the study intervention, compensation or necessary medical support will be provided in compliance with institutional policies and applicable regulations. All SAEs will be reported to the IRB in a timely manner, in accordance with established reporting requirements.

### Adverse events

2.9

The pharmacopuncture solution used in this study contains salmon-derived PDRN, a substance reported to exert anti-inflammatory and tissue-regenerative effects in various musculoskeletal conditions (16). Although PDRN pharmacopuncture is widely utilized in primary care settings and is generally considered safe, mild adverse reactions such as bruising, localized discomfort, or transient fatigue may occur; therefore, these possibilities will be explained to participants in advance.

The magnetic needle used in this study is inserted into deep tissue layers under ultrasound guidance. Similar to other acupuncture-based procedures, potential adverse reactions may include localized pain or tenderness at the insertion site, transient paresthesia (such as tingling, prickling, or burning sensations), minor bleeding or hematoma, and, less frequently, skin hypersensitivity, infection, dizziness, syncope, nausea, or headache.

To ensure participant safety, all adverse events will be assessed immediately after the procedure and reassessed 24–36 h later via telephone or mobile follow-up. If an adverse event occurs, investigators will promptly report it to the principal investigator. In cases where a SAE is suspected, appropriate clinical care will be provided immediately in accordance with institutional medical protocols.

All adverse events will be documented in the CRF, including symptom characteristics, onset date, duration, severity, and potential causal relationship to the intervention. SAEs will be reported to the IRB according to institutional reporting requirements. Upon study completion, adverse event data will be summarized descriptively by frequency, type, and incidence within each study group for safety evaluation.

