## Abstract

**Background/Objectives:**

Acute Low Back Pain (LBP) commonly shows rapid symptom improvement during the early phase; however, delayed or inadequate treatment may increase the risk of recurrence and chronicity. Ultrasound-guided pharmacopuncture has demonstrated promising analgesic effects, yet the optimal needle length for deep interfascial targeting remains unclear, particularly in procedures involving the Quadratus Lumborum–Psoas–Iliocostalis (QPI) space. This study aims to compare the short-term clinical response, procedural feasibility, and safety of short versus long needles used for QPI-guided pharmacopuncture in patients with acute LBP.

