Based on these clinical needs and previous findings, the present study aims to compare the immediate analgesic effects of short versus long needles in ultrasound-guided pharmacopuncture targeting the QPI space through a prospective, multicenter observational design. The primary outcome is the change in pain intensity immediately after treatment, enabling evaluation of how needle length influences the acute-phase clinical response. Additionally, secondary procedural and exploratory metrics—including deep-plane reachability, technical usability, and safety—will be assessed to explore the feasibility and potential for standardizing deep ultrasound-guided pharmacopuncture in primary care Korean medicine settings.

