### Study design

2.1

This prospective, multicenter, comparative observational study aims to evaluate whether needle length (Long versus Short) influences procedural usability, deep target achievement rate, clinical effectiveness, and safety during ultrasound-guided pharmacopuncture for acute LBP. The intervention targets the interfascial plane formed by the QL, PM, and IC muscles—referred to as the “QPI space.” The anatomical location and ultrasound appearance of the QPI interfascial space are illustrated in Figure 1. All procedures are performed under real-time ultrasound guidance. Polydeoxyribonucleotide (PDRN) derived from salmon is used as the pharmacological agent, and a magnetic needle–guided tracking system is applied to deliver 1–2 mL of the injectate into the target layer.

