#### Sample size calculation

2.6.1

Since no prior study has been conducted under conditions identical to the present trial, the effect size for this study was estimated based on comparable interventions and studies reporting changes in NRS or VAS as primary outcomes. In a double-blind randomized controlled trial evaluating pharmacopuncture in patients with chronic LBP, the mean reduction in pain after 3 weeks was 2.74 points in the treatment group and 1.76 points in the control group, yielding an estimated between-group difference of approximately 1.0 point and a Cohen’s d of approximately 0.56 (23). Similarly, a systematic review of acupuncture for acute LBP reported a mean difference of −1.75 points on the VAS compared with controls (95% CI: −2.39 to −1.12) (24), indicating a meaningful short-term analgesic benefit. Additionally, a single-arm study conducted in Japan evaluating ultrasound-guided hydrodissection demonstrated a reduction of more than 4 points on the VAS immediately after the procedure (25), suggesting that ultrasound-guided interventions may provide rapid short-term pain relief.

Additionally, although the Minimum Clinically Important Change (MCIC) for acute LBP has been reported to be approximately 3.5 points on the NRS scale (26), such thresholds primarily apply to single-arm studies evaluating absolute symptom improvement. In comparative trial designs, such as the present study, the full magnitude of the MCIC is not required to determine a meaningful treatment difference. Instead, between-group differences of approximately 1 point—similar to those reported in previous randomized controlled trials—may still represent a clinically relevant effect when assessing comparative therapeutic outcomes.

Based on the literature reviewed, the effect size for this study was set at Cohen’s d = 0.56. Using a two-sample *t*-test with a significance level of 0.05 and a statistical power of 80%, the minimum required sample size was calculated to be 104 participants (52 per group). Allowing for an anticipated dropout rate of approximately 10%, the final target sample size was set at 120 participants, with 60 allocated to the short-needle group and 60 to the long-needle group.

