#### Statistical analysis

2.6.2

All statistical analyses will be performed using R software (version 4. X. X; R Foundation for Statistical Computing, Vienna, Austria). All tests will be two-tailed, with statistical significance defined as *p* < 0.05. Continuous variables will be summarized as mean ± standard deviation or median with Interquartile Range (IQR), depending on the data distribution. Categorical variables will be presented as frequencies and percentages.

For the primary outcome, changes in NRS scores will be analyzed according to the data distribution. Between-group comparisons will be performed using an independent *t*-test if the normality assumption is satisfied; otherwise, the Wilcoxon rank-sum test will be used. Within-group changes will be assessed using a paired *t*-test or the Wilcoxon signed-rank test, depending on whether the data meet normality assumptions.

For the secondary outcomes, changes in lumbar ROM from baseline will be analyzed using the same statistical methods applied to the primary outcome. Between-group comparisons will be conducted using an independent *t*-test or the Wilcoxon rank-sum test, while within-group comparisons will be analyzed using a paired *t*-test or the Wilcoxon signed-rank test, depending on data normality.

The ODI will be categorized into predefined functional disability levels, and differences in distribution between groups will be analyzed using the Chi-square test or Fisher’s exact test, as appropriate.

PRPPR will be assessed immediately after treatment and again at 24–36 h post-intervention. Between-group comparisons will be conducted using an independent *t*-test or the Wilcoxon rank-sum test, while within-group comparisons will be analyzed using a paired *t*-test or the Wilcoxon signed-rank test, depending on the data characteristics.

In addition, procedural characteristics and usability-related variables associated with needle length—including deep-layer reach success rate, number of insertions, procedure time, and operator usability score—will be summarized using descriptive statistics. When appropriate, exploratory between-group comparisons will be conducted using the Mann–Whitney U test or the Chi-square test. These analyses will serve as supportive reference analyses and will not directly influence the interpretation of the primary clinical outcomes.

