## Discussion and conclusion

3

This study is a prospective, multicenter observational protocol designed to evaluate the feasibility and short-term clinical response of ultrasound-guided pharmacopuncture targeting the interfascial QPI space in patients with acute LBP in a primary care setting.

Recently, interest in ultrasound-guided acupuncture and pharmacopuncture has grown within Korean musculoskeletal clinical practice, and related studies have gradually emerged (27, 28). However, significant heterogeneity in study design, target tissue layers, pharmacological formulations, and outcome measures has hindered the establishment of consistent clinical standards (29–31). Notably, prospective research investigating interfascial QPI-space approaches in patients with acute LBP remains extremely limited, with existing literature largely restricted to retrospective case reports (7). Accordingly, this study provides preliminary feasibility-level clinical evidence and serves as an exploratory step toward evaluating the therapeutic and procedural relevance of this technique.

A key strength of this study is its design, which directly compares how differences in needle length (Short versus Long) affect both procedural performance and short-term clinical response within a single standardized intervention—ultrasound-guided pharmacopuncture targeting the interfascial QPI space. Unlike previous studies that primarily reported clinical outcomes or provided case-based descriptions using a single needle length, this study systematically collected procedural data, enabling evaluation of technical factors such as needle-tip visibility during deep advancement, accessibility of the target layer across different body habitus, operator handling characteristics, and perceived procedural difficulty. This approach extends beyond a simple comparison of clinical efficacy and enables a more comprehensive assessment of the reproducibility and practical feasibility of deep interfascial access, thereby distinguishing this study from prior literature.

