The interfascial plane of the lumbar region can present varying levels of technical difficulty depending on factors such as body habitus (including BMI and muscle thickness), probe–needle alignment, acoustic properties, and anatomical variations. Anatomical and imaging studies indicate that the target layer is typically located at a depth of approximately 4–6 cm or more from the skin surface (32). Given this depth, conventional 50–60 mm needles may provide limited access or an insufficient safety margin in patients with increased soft tissue thickness. In contrast, anesthesia literature shows that 80–100 mm block needles are routinely used for similarly deep interfascial approaches, such as QL or Erector Spinae Plane (ESP) blocks (33–37). However, within Korean medicine clinical practice, systematic validation of long-needle use—particularly regarding safety, reproducibility, and ultrasound visibility—has been limited, resulting in selective or restricted adoption in real-world settings. Accordingly, the design of the present study holds both methodological and clinical relevance by addressing this gap and evaluating the feasibility of long-needle application in ultrasound-guided interfascial pharmacopuncture.

This study has several methodological strengths, including its prospective design, needle-length comparison framework, multicenter real-world data collection, and incorporation of practitioner usability assessments. Notably, the study was designed to collect not only clinical response outcomes but also procedural variables such as needle handling experience, perceived technical difficulty, and confidence in reaching the target plane. This approach enables exploration of the relationship between therapeutic outcomes and procedural experience. Furthermore, conducting the study in a real-world outpatient clinical setting enhances the applicability of the findings, as it reflects variability in patient characteristics, procedural accessibility, and the operator learning curve. These features contribute to the study’s potential value for future clinical implementation and the development of educational frameworks.

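### The aim is to compare safety between needles, but the adverse event analysis is fixed as within-group description with no contrast or measure of uncertainty (minor mismatch)

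*Protocol article*

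**What the plan says.** The comparative aim appears twice. The Abstract says "This study aims to compare the short-term clinical response, procedural feasibility, and safety of short versus long needles", and section 2.1 (Study design) says the study "aims to evaluate whether needle length (Long versus Short) influences procedural usability, deep target achievement rate, clinical effectiveness, and safety".

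Section 2.9 (Adverse events) gives the one stated safety analysis: "adverse event data will be summarized descriptively by frequency, type, and incidence within each study group for safety evaluation".

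Section 2.6.2 (Statistical analysis) specifies between-group tests for pain, range of motion and patient-reported percentage pain reduction. For the procedural variables it says that "deep-layer reach success rate, number of insertions, procedure time, and operator usability score—will be summarized using descriptive statistics", and it then allows exploratory between-group comparisons where appropriate. Adverse events are not on that list. Confidence intervals are promised only for adjusted effects, and only if baseline differences are found.

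On rank and scope, the Introduction says that "secondary procedural and exploratory metrics—including deep-plane reachability, technical usability, and safety—will be assessed to explore the feasibility". Section 2.5 does not list safety as an outcome, and the Discussion says "this study provides preliminary feasibility-level clinical evidence".

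**The concern.** Section 2.1 names four things that needle length may influence. Three of them (usability, reaching the deep target, clinical effectiveness) have a between-group analysis in section 2.6.2, although for the first two it is conditional and exploratory. The fourth, safety, is fixed as description inside each group. An analysis that follows section 2.9 to the letter yields two columns of counts, with no estimate of the difference and nothing to show how much the sample leaves open.

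This matters because few events are to be expected in a single-session study of this size. Two short columns of small or zero counts are easily taken as reassurance about the longer needle, and the Introduction and Discussion give limited safety evidence as one reason why that needle is not widely used. An interval would show how far such reassurance goes.

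**Working it through.** **Plan's own figure.** Section 2.6.1 sizes the study on pain: "the effect size for this study was set at Cohen’s d = 0.56", two-sided alpha 0.05, power 80%.
- Normal approximation: n = 2(1.960 + 0.842)² / 0.56² = 2 × 7.85 / 0.3136 = 50.1, rounded up to 51 per group.
- The noncentral t solution is 51.03, rounded up to 52 per group, or 104 in total. This matches the plan.
- With 10% dropout, 104 / 0.9 = 115.6, rounded up to 116. The target of 120 (60 per group) covers this.

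The sample size is sound on its own terms but says nothing about adverse events.

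**Inputs for safety.** There are 60 per group (section 2.6.1). The document gives no adverse event rate, so every count and rate below is an assumption, chosen to show a range.

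**One group, zero events.** The exact (Clopper-Pearson) two-sided 95% upper limit is 1 − 0.025^(1/n).
- n = 60: 1 − 0.025^(1/60) = 5.96%.
- n = 54 (60 less 10%): 6.60%.

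The second line is relevant to delayed events. Section 2.3.4 does not count a missed 24–36 h contact as dropout, so the number of participants with delayed-event data may be below 60.

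**Probability of seeing nothing.** For a reaction with true risk p this is (1 − p)^60. At p = 2%, 0.98^60 = 0.30. At p = 1%, it is 0.55.

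**Difference between groups.** The Newcombe 95% interval is built from each group's Wilson limits (l, u), with d = p1 − p2:
- lower limit: d − √[(p1 − l1)² + (u2 − p2)²]
- upper limit: d + √[(u1 − p1)² + (p2 − l2)²]

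For 3/60 in each group, the Wilson limits are 1.7% and 13.7%. The half-width is √[(0.050 − 0.017)² + (0.137 − 0.050)²] = 0.093.

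| Assumed counts (each of 60) | Difference, points | 95% interval, points |
|---|---|---|
| 0 v 0 | 0 | −6.0 to +6.0 |
| 3 v 3 | 0 | −9.3 to +9.3 |
| 6 v 6 | 0 | −11.5 to +11.5 |
| 5 v 2 | +5.0 | −4.3 to +15.0 |

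**Why an interval and not a test.** Exact Fisher power at 60 per group is 33% for assumed true risks of 5% v 15%, and 28% for 2% v 10%. A non-significant result would tell the reader little.

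**Limit of these intervals.** They treat participants as independent and the groups as comparable. Sections 2.1 and 2.3.2 assign two clinics to each needle, so needle is fully nested in clinic. Differences between clinics and operators can move the estimate in either direction, and the intervals are likely too narrow for a needle effect.

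**The case against.** The strongest case against is that this is ordinary practice. Adverse event tables by group are usual when the sample is sized on an efficacy outcome. The choice of contrast or interval commonly belongs in the analysis plan, to which section 2.3.6 refers and which is not shown. That stands: a missing interval alone would be no finding. What remains is internal to the document. It sets a comparative aim and then states an analysis that does not address it.

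A reader might infer that the study will declare the two needles equally safe. The document does not support this. It never mentions equal safety or non-inferiority, it ranks safety as exploratory, and it calls its evidence preliminary. The Discussion refers to limited earlier validation of long-needle safety, but its own claim is more modest: "evaluating the feasibility of long-needle application in ultrasound-guided interfascial pharmacopuncture".

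A reader might also infer that the safety aim cannot be answered at all from the planned output. That goes too far. Two group incidences give the crude difference by subtraction and, with the denominators, an interval. The imprecision comes from the sample size, and reporting an interval shows it without reducing it.

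Nor is safety treated quite as differently as it first seems, since the procedural variables are also described first and compared only where appropriate. But they share safety's exploratory rank and still have a route to a comparison. Exploratory status therefore argues against powering or testing for safety, and not against an estimate with its uncertainty.

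**Conclusion.** The point holds as a minor mismatch. The Abstract and section 2.1 promise a comparison of safety, while section 2.9 fixes only a within-group description. At 60 per group, zero events is compatible with a risk of up to about 6.0% for each needle, and equal counts of 0 v 0 or 3 v 3 leave a difference of about 6 to 9 points either way. The first figure depends only on the group size and on every participant being assessed. The second rests on assumed counts. Any contrast is also confounded with clinic, so even a reported interval would not isolate needle length. The plan does not claim that it will show equal safety, and the point should not be read as saying that it does.

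**What to change.** In section 2.9:
- Give the proportion of participants with at least one adverse event in each group with an exact 95% confidence interval, stating the upper limit when there are no events.
- Give the risk difference between needles with a 95% confidence interval (Newcombe, for example). Label it exploratory, unadjusted for site and confounded with clinic and operator, and note that the interval is likely too narrow for a needle effect.
- Keep individual reactions descriptive. Separate contrasts for each listed reaction would be sparse and numerous.
- For delayed events, use the participants actually reached at 24–36 h as the denominator, and show that number.
- State that few or no events does not show equal safety.

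The alternative is to leave section 2.9 as it is and reword the safety aim in the Abstract and section 2.1 as descriptive.

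The cost of the first option is a few sentences, two table columns and a slightly less favourable safety statement. The second costs a change to two sentences and gives up the comparative safety aim. Neither needs new data, and either is best settled before results are known.
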